### Study drugs

#### Prograf^®^ and Envarsus

Prograf^®^ and Envarsus^®^ contain the active ingredient tacrolimus. Tacrolimus is an immunosuppressive drug that reduces T-cell activity by binding to a cytosolic protein (FKBP12); it specifically and competitively inhibits calcineurin, leading to a calcium-dependent inhibition of T-cell signaling pathways (14, 15).

Prograf^®^, the immediate-release formulation of tacrolimus, exhibits significant inter- and intra-individual variability in absorption due to interactions with food and concomitant medications and the cytochrome P-450 system, which is subject to functional polymorphisms. In addition, Prograf^®^ has rather low bioavailability due to poor water solubility and pre-systemic gastrointestinal metabolism (16, 17). In humans, tacrolimus has been shown to be absorbed throughout the gastrointestinal tract. Available tacrolimus is generally absorbed rapidly.

Envarsus^®^ is a prolonged-release formulation of tacrolimus and was approved by the European Medicines Agency (EMA) in 2014. It is currently indicated for the prophylaxis of transplant rejection in adult kidney or liver allograft recipients and treatment of allograft rejection in adult patients refractory to other immunosuppressive drugs but, to date and in contrast to Prograf^®^, it has not been officially licensed for use in children. The prolonged-release formulation results in an extended oral absorption profile with an average time to maximum blood concentration (C_max_) of approximately 6 hours (t_max_) at a steady state. The oral bioavailability of Envarsus^®^ is approximately 40% higher than the same dose of the immediate-release tacrolimus formulation Prograf^®^ in kidney transplant patients (18). There is a strong correlation between AUC0-24 and steady-state whole blood trough levels for Envarsus^®^. Therefore, monitoring of whole blood trough levels provides a good estimate of systemic exposure (19).

In the systemic circulation, tacrolimus binds strongly to erythrocytes resulting in an approximately 20:1 distribution ratio of whole blood/plasma concentrations. In plasma, tacrolimus is highly bound (>98.8%) to plasma proteins, mainly to serum albumin and α-1-acid glycoprotein (20). The half-life of tacrolimus is comparatively long and variable. In healthy subjects, the mean half-life in whole blood is approximately 30 hours (21). It was found that, following intravenous and oral administration of ^14^C-labeled tacrolimus, most of the radioactivity was excreted in the feces (22).

Tacrolimus has a narrow therapeutic index. Tacrolimus levels below this recommended range carry the risk of graft rejection, while levels above the range are associated with increased toxicity such as opportunistic infections, nephrotoxicity, diabetes, tremor, hypertension, and malignancies (23–25). The improved bioavailability of Envarsus^®^, which allows once-daily dosing, results in lower inter- and intra-patient variability of drug absorption, with reduced peak-to-trough fluctuation and earlier achievement of a stable tacrolimus profile, as demonstrated in healthy volunteers (26). Envarsus^®^ shows an improved pharmacokinetic profile compared to Prograf^®^ with significantly lower peak levels. Therefore, it may be advantageous in terms of toxicity (27).

Regarding the high intra- and inter-patient variability of tacrolimus, increasing clinical evidence suggests that gut bacterial drug metabolism may play a crucial role (28, 29). Experimental results from our group demonstrated tacrolimus metabolization by ubiquitous bacterial species *in vitro* and showed that some strains could even metabolize up to 85% of the parent drug concentration (30). As explained above, the MeltDose™ drug delivery technology of Envarsus^®^ results in higher bioavailability and more consistent pharmacokinetics. This is partly explained by the predominant release in the colon, where the prevalence of CYP3A is significantly lower than in the small intestine (31). As a result, the pre-systemic elimination of Envarsus^®^ due to CYP3A metabolism is significantly reduced. As with the identification of pharmacogenetic factors, the stool microbiome might lead to a potential paradigm shift in the pharmacokinetics of tacrolimus and its respective drug formulations.

### Inclusion/exclusion criteria

A total number of 30 Caucasian male or female children at four German study sites will be enrolled in this clinical trial. They will be enrolled if they meet the inclusion/exclusion criteria listed in **Table 1**. Dynamic randomization according to the method proposed by Signorini will be used to assign patients to the respective arm. The study will be randomized with a probability of 50:50. The total study duration (first patient first visit (FPFV) to last patient last visit (LPLV)) will be approximately 20 months, including a recruitment period of around 18 months. The study duration per patient will be approximately 9 weeks from visit 1.

**Table 1 T1:** Selection criteria.

**Inclusion Criteria**
1. Pediatric kidney transplant recipients (single-organ recipients).
2. Aged ≥ 8 years but ≤ 18 years who are receiving tacrolimus (Prograf^®^) therapy and who are able to swallow tablets with a minimum dose of 0.75 mg/day Envarsus^®^.
3. At least 6 months after transplantation.
4. Stable kidney function (delta eGFR < 10 ml/min/1.73 m^2^ (CKiD formula) over the last 3 months.
5. Women of childbearing potential who are practicing complete abstinence from sexual intercourse (periodic abstinence and withdrawal are not acceptable) or who have a sexual relationship with female partners only and/or with sterile male partners; or women of childbearing potential who are sexually active with a fertile male partner, who have a negative pregnancy test during screening and who agree to use reliable methods of contraception from the time of screening, during the study and for a period of 4 weeks following the last administration of study medication; or women without childbearing potential defined as females before menarche or at least 6 weeks after surgical sterilization by bilateral tubal ligation or bilateral oophorectomy or hysterectomy or uterine agenesis.
6. Patient/parents/legal guardian(s) must be capable of understanding the purpose and risks of the study.
7. Signed informed consent was obtained by the patient and parents/legal guardians.
**Exclusion Criteria**
1. Coefficient of variation of tacrolimus trough levels > 0.35 over the previous 6 months.
2. Pregnancy/breastfeeding.
3. Unstable kidney function.
4. Hypersensitivity to any of the components of the medications used.
5. Not eligible for any reason according to the investigator’s evaluation.
6. Known positive HIV-1 or HCV test.
7. Participation in another clinical trial (other investigational drugs or devices at the time of enrollment or within 30 days prior to enrollment).

### Sample size calculation

The expected ratio of the geometric means of the AUC of Envarsus^®^ vs. Standard tacrolimus is 0.9749. The standard deviation of the coefficient of variation is calculated as 0.303 derived from the corresponding CI (32). The variation coefficient (as the ratio of expected ratio and standard deviation) is then assumed as 0.311. With a two-sided standard error of 10% and the equivalence limits of 0.8 and 1.25 (corresponding to the EMA guideline), a sample size of 27 is calculated to reach a power of 80%. With a dropout of 10%, 30 patients are therefore required.

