### Statistical methods

The primary objective of the study is to demonstrate the equivalency between total exposure and trough levels of both Prograf^®^ and Envarsus^®^ (with a daily dose conversion factor of 0.7) in compliant patients without any protocol deviations. Therefore, the primary endpoint is the full AUC0-24 of tacrolimus levels over 24 hours. The objective is to demonstrate that the 90% confidence interval for the ratio of the full AUC0-24 of Envarsus^®^ (with a conversion factor of 0.7 for the daily dose) to Prograf^®^ is within the acceptance interval of 0.8 - 1.25 (33). This interval has been chosen in accordance with the German Federal Institute for Drugs and Medical Devices. As a secondary analysis, whether the confidence interval is also within the narrower interval of 0.9 to 1.11 recommended for drugs with a narrow therapeutic index (NTI) will be checked (33).

Demographic and baseline characteristics will be summarized as absolute and relative frequencies (for categorical outcomes), median and interquartile ranges (IQR), or arithmetic means and standard deviation. Pharmacokinetic measures will be summarized as median, geometric mean, arithmetic mean and standard deviation, minimum and maximum, and coefficient of variation. The primary endpoint – full AUC0-24 – will be calculated from tacrolimus measurements after administration of the respective medication by linear interpolation between measurement time points (see **Supplementary Material**). It will then be analyzed using an ANOVA model on the log-transformed AUC0-24 values comparing Prograf^®^ and Envarsus^®^ with sequence, subject within sequence, and period as further fixed factors as suggested by the EMA guideline (33). A summary of the assessment of the primary objective in terms of the estimand framework is given in the **Supplementary Material**.

In addition to full AUC0-24 analysis, the following pharmacokinetic parameters will form part of the evaluation: C_0_, C_max_, t_max_, and their corresponding coefficients of variation. Pharmacokinetic half-life and apparent clearance after oral administration of Envarsus^®^ and Prograf^®^ will be evaluated accordingly. Pearson’s correlation coefficients will be used to assess suitability and trough levels and AUC0-24 will be correlated.

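### The stated 27 patients for 80% power does not follow from the stated inputs under the 90% confidence interval rule: power is about 65% if 0.311 is a within-subject CV, about 94% if 0.303 is the SD of the paired log ratio

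*Protocol article*

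**What the plan says.** The Sample size calculation section of the protocol article gives these inputs:

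- Ratio: "The expected ratio of the geometric means of the AUC of Envarsus^®^ vs. Standard tacrolimus is 0.9749".
- SD: "The standard deviation of the coefficient of variation is calculated as 0.303 derived from the corresponding CI (32"), where 32 is the citation number of the source.
- CV: "The variation coefficient (as the ratio of expected ratio and standard deviation) is then assumed as 0.311".
- Level and limits: "With a two-sided standard error of 10% and the equivalence limits of 0.8 and 1.25".

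From these it concludes that "a sample size of 27 is calculated to reach a power of 80" per cent, and it raises 27 to 30 for a 10% dropout.

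The Statistical methods section sets the decision rule: "The objective is to demonstrate that the 90% confidence interval for the ratio of the full AUC0-24" of Envarsus to Prograf lies inside 0.8 to 1.25. For the model, the same section has the endpoint "analyzed using an ANOVA model on the log-transformed AUC0-24 values comparing Prograf^®^ and Envarsus^®^ with sequence, subject within sequence, and period". All of these terms enter as fixed effects. The primary comparison is limited to compliant patients without protocol deviations.

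**The concern.** A two-sided 10% level and a 90% confidence interval are the same rule: two one-sided tests at 5% each. The two sections therefore agree on the level, and the stated power should be reproducible from the stated inputs at 5% per side. It is not.

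The power of the primary endpoint is at stake. If the true figure is nearer 65% than 80%, the chance of missing equivalence under the plan's own assumptions is about 35% rather than 20%, and a confidence interval that misses the limits would say less about non-equivalence than the published 80% suggests. If the true figure is nearer 94%, the sample size is larger than its own justification supports. The wording does not let a reader tell which applies, because it never says whether the SD is within-subject or belongs to the paired ratio.

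**Working it through.** **Inputs.** From Sample size calculation: ratio 0.9749, SD 0.303, CV 0.311, limits 0.8 and 1.25, n = 27. From Statistical methods: 90% interval, crossover ANOVA on log AUC. Allocation is 1:1 (Inclusion/exclusion criteria), so I take sequences of 13 and 14 at n = 27.

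**The CV.** 0.303 / 0.9749 = 0.311, so the figure is SD divided by ratio. The text describes the inverse, and 0.9749 / 0.303 = 3.22.

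**Method.** Exact power of two one-sided t-tests on the log scale, averaged over the chi-square distribution of the variance estimate:

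- σ_w = √ln(1 + CV²) = √ln(1 + 0.311²) = 0.304
- SE = σ_w · √(½ · (1/n₁ + 1/n₂)) = 0.304 · √(½ · (1/13 + 1/14)) = 0.0828
- df = n − 2 = 25
- Equivalence is declared if the estimate ± t · SE (SE estimated from the data) lies within ±0.223, since ln 0.8 = −0.223 and ln 1.25 = +0.223
- The assumed true value is ln 0.9749 = −0.025, so the distance to the nearer limit is 0.223 − 0.025 = 0.198

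**Reproducing 27.** With 10% per side (an 80% interval), t = 1.316 and the half-width is about 1.316 × 0.0828 = 0.109. Power is 79.4% at n = 26 and 81.0% at n = 27. So 27 is exactly the smallest n reaching 80% at that level.

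**The planned rule.** With 5% per side (a 90% interval), t = 1.708 and the half-width is about 1.708 × 0.0828 = 0.141.

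| Evaluable n | Power, 5% per side (90% interval) | Power, 10% per side (80% interval) |
|---|---|---|
| 26 | 62.6% | 79.4% |
| 27 | 65.0% | 81.0% |
| 30 | 71.8% | 85.2% |
| 34 | 78.8% | 89.4% |
| 35 | 80.2% | 90.2% |
| 36 | 81.6% | 91.0% |

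Simulation agrees with the exact values at n = 27 (about 65% and 81%). To reach 80% at n = 27 under the 90% interval, the CV would have to be about 0.27 or lower.

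**Sensitivity, still as a within-subject quantity (n = 27, 5% per side).** 0.303 used directly as the log SD gives 65.4%; 0.311 used directly gives 62.1%; a CV of 0.303 gives 68.1%; a true ratio of 1.0 with CV 0.311 gives 67.2%.

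**Paired reading.** If 0.303 is the SD of each patient's log ratio, SE = 0.303 / √27 = 0.0583. Power at n = 27 and 5% per side is then about 94%. It is just under 80% at 18 patients and about 82% at 19, so 19 would suffice.

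**Dropout step.** 27 / (1 − 0.10) = 30, as stated.

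**The case against.** The strongest objection is that the 65% is conditional. The section never says within-subject or intra-individual. It says the SD was derived from a confidence interval in a cited source and then relates that SD to the expected ratio. An SD worked back from the interval of a ratio by √n would be the SD of the patient-level ratio, and dividing it by the ratio fits that reading. The trial would then have more power than claimed, not less. The source interval is not in the document, so this cannot be settled from it. This objection stands. It bars the flat statements that a reader might infer: that the trial has 65% power, that the risk of missing equivalence is 35%, or that 80% power at 27 is attainable only with an 80% interval. The paired reading does not rescue the stated figure, however, because 27 would not then be the number needed for 80%.

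A second objection is that 10% per side is not the only route to a number near 27. A paired calculation on the untransformed scale at 2.5% per side needs about 26 to 28 patients, depending on the SD used. That route contradicts the stated 10% level, the 90% interval and the log-scale model, so it is a weaker explanation. Still, an exact match at 27 does not prove how the figure arose.

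Third, calling the level a standard error and inverting the CV ratio change no number. That is so; they are clerical.

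**Conclusion.** The stated power is wrong as written. No reading examined gives 27 as the number needed for 80% power under the trial's own rule of a 90% interval on the log scale. The size and direction of the error depend on what 0.303 is:

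- **Within-subject** (the usual input for a crossover bioequivalence calculation, and favoured by the text calling 0.311 a coefficient of variation): power is about 65% at 27 evaluable and 72% at 30, with 35 evaluable needed for 80%. Across readings of 0.303 and 0.311 on the log scale, power at 27 is 62% to 68%.
- **SD of the paired log ratio**: power is about 94% at 27, with 19 sufficient.

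That 10% was spent on each one-sided test is the likely cause under the first reading, but it remains an inference. These figures take the plan's ratio of 0.9749 as true and assume near-equal sequences. The 27 counts evaluable patients; if exclusions for protocol deviations leave fewer, power falls on either reading.

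**What to change.** Restate the Sample size calculation section:

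1. Say whether 0.303 is the within-subject SD or the SD of the within-patient log ratio, and how it was obtained from the source interval.
2. State that each one-sided test is at 5%, matching the 90% interval in Statistical methods.
3. Recompute and print the resulting power: about 65% at 27 evaluable and 72% at 30 if within-subject (adding that 80% is reached at 27 only if the CV is at most about 0.27), or about 94% at 27 if paired.
4. Write the CV as SD divided by ratio, and replace the term standard error with significance level.

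The cost is a wording change and, on the within-subject reading, a less favourable published power. Enrolment and conduct stay as they are. The article reports four patients enrolled by September 2023, so at that stage the correction could be made well before results.

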### Study assessments

Patients will be seen and evaluated according to the flow chart given in **Table 2**. At the time of enrollment, participants are treated with Prograf^®^ to prevent transplant rejection. Patients will be monitored regularly in the outpatient clinic. In this way, potentially eligible patients will be identified during routine outpatient visits.

**Table 2 T2:** Flow chart of study visits.

Phase	0 Screening	1 Baseline	2a Build-up period	2b Sequence 1 (A) or 2 (B) *(hospital stay for AUC0-0-24^6^)*	3a Build-up period	3b Sequence 2 (A) or 1 (B) *(patients hospitalized for AUC0-24^6^)*	4
**Duration**	Within 6 weeks before baseline	1 day (Day 1)	4 days (Day 2-5)	4 weeks /Day 6-33)	4 days (Day 34-37)	4 weeks (Day 38-65)	11 days (Day 66-76)
**Visits**	Screening-Visit	Baseline-Visit	Build-up-Visit 1	AUC0-24 Visit 1 (Hospital stay^6^)	Build-up-Visit 2	AUC0-240 Visit 2 (Hospital stay^6^)	End of study Visit
**Day of visits**		Day 1	Day 4 (+/- 1 day)	Day 19 (+/- 7 days)	Day 36 (+/- 1 day)	Day 51 (+/- 7 days)	Day 71 (+/-5 days)
Informed Consent	✓						
Inclusion/ Exclusion Criteria	✓						
Randomization		✓					
Physical Examination^1a^		✓	✓	✓	✓	✓	✓
Baseline Characteristics^1b^		✓					
Blood Values^2a^		✓	✓	✓	✓	✓	✓
Urine Values^2b^		✓	✓	✓	✓	✓	✓
Urine Pregnancy Test		✓	✓	✓	✓	✓	✓
Urine Volume 24h^2c^		✓		✓		✓	
Full AUC0-240-240-24^2d^ (serial blood samples at 0, 1.5, 2, 4, 6, 8, 12, 13.5, 14, 16, 20, 24 h)				✓		✓	
Pharma-cogenetic Analysis^2e^		✓					
Trough Levels^2f^				✓			
Microbiome Analysis (feces, urine, blood)^2d^		✓		✓		✓	✓
Study Drug Dispensing		✓		✓			
Switch to other Immunosuppres-sant^3^			✓ (Day 2)		✓ (Day 34)		
Concomitant Medication		✓	✓	✓	✓	✓	✓
Envarsus^®^ Return^4^					✓ (for Group A)		✓ (for Group B)
Adverse Events^5^	✓	✓	✓	✓	✓	✓	✓

^1a^Complete physical examination, vital signs (blood pressure, pulse), weight, height, date, and time of visit.

^1b^Medical history including underlying disease, date of transplantation, type of transplantation (living donation/deceased donation), preemptive transplantation (yes/no), gender, date of birth, and clinical assessment.

^2a^Blood values: blood gas analysis, creatinine, urea, LDH, cystatin C, eGFR (CKiD formula), HLA and non-HLA-DSA, ALT, yGT, CK, HbA1c, hematology (incl. differential blood count), electrolyte (potassium, calcium, phosphate, magnesium), CRP, and tacrolimus trough level.

^2b^Urine Values: Urea, glucose, creatinine, and albumin.

^2c^Urine Volume: 24h collection urine.

^2d^Full AUC0-240-240-24: Patients need to be hospitalized for the sampling of blood (9.5 ml whole blood per patient) to determine tacrolimus levels; time = 0 is defined as 12 hours after the last intake of Prograf^©^/24 hours after the last intake of Envarsus^©^. Pharmacokinetic Analysis: 0.5 ml whole blood (EDTA) per sampling point (0.0, 1.5, 2.0, 4.0, 6.0, 8.0, 12.0, 13.5, 14.0, 16.0, 20.0, and 24.0 h) to be stored at -20° C until shipping (to be shipped frozen to Cologne, Labor für Therapeutisches Drug Monitoring. Pharmacodynamic Analysis: 0.5 ml whole blood (lithium-heparin) per sampling point (0.0, 1.5, 2.0, 4.0, 6.0, 20.0, and 24.0 h) to be stored at room temperature and to be shipped later the same day to Heidelberg Institute of Human Genetics.

^2e^Pharmacogenetic Analysis: At baseline visit 1 ml whole blood (EDTA) for pharmacogenetic analysis (to be shipped at room temperature.

^2f^Trough (C_0_) levels: defined as 12 hours after the last intake of Prograf^©^/24 hours after the last intake of Envarsus^©^. 0.5 ml whole blood (EDTA) to be stored at -20° C until shipping (to be shipped frozen).

^2g^Microbiome Analysis: fecal samples: metagenomic-/transcriptomic analysis and metabolomics; urine and blood samples: metabolomics.

^3^In phase 3b, patients will be switched to the other immunosuppressant for 4 weeks.

^4^Patients must return the unused Envarsus^®^ for accountability and destruction of unused tablets at Visit 3a for Group A and also at Visit 4 for Group B.

^5^The adverse event documentation period for this trial begins with informed consent and ends with the last study visit.

^6^Patient hospitalizations must happen from Monday to Wednesday as samples for pharmacodynamic analysis must be shipped immediately within 1 day and must reach the central lab in Heidelberg on Thursday at the latest.

A complete physical examination including vital signs (blood pressure and pulse), weight, height, date, and time of visit will be documented at each visit. Screening evaluations will be performed within 6 weeks prior to the baseline evaluation to determine the patient’s eligibility to participate in the study. At each visit, the following laboratory measurements will be performed at the local laboratory: Cystatin C, eGFR (CKiD formula), hematology (including differential blood count), electrolyte (potassium, calcium, phosphate, and magnesium), human leukocyte antigen (HLA) and non-HLA-DSA, alanine aminotransferase (ALT), gamma-glutamyl transferase (yGT), creatine kinase (CK), hemoglobin A1c (HbA1c), blood gas analysis, creatinine, urea, hematology, electrolytes, lactate dehydrogenase (LDH), C-reactive protein (CRP), and tacrolimus trough level, and in urine: urea, glucose, creatinine, and albumin including pregnancy test. Tacrolimus trough levels (C_0_) will be determined at 12 hours after the last intake of Prograf^®^ or 24 hours after the last intake of Envarsus^®^, respectively. Some special analyses will be carried out in the central laboratory in Cologne (pharmacokinetics; Laboratory for Therapeutic Drug Monitoring, University Hospital of Cologne, Germany) and Heidelberg (pharmacodynamics; Institute of Immunology, University Hospital of Heidelberg, Germany). The pharmacodynamic analysis will be based on the residual expression of NFAT-regulated genes. Gut microbiome analyses will be performed at the European Molecular Biology Laboratory (EMBL) in Heidelberg. Fecal samples will be collected at home 0-48 hours prior to the scheduled visit. Information on concomitant medication use is documented for each patient. Envarsus^®^ (prolonged-release tablets containing tacrolimus (0.75, 1.00, or 4.00 mg)) should be taken orally once daily in the morning on a fasting state at 24-hour intervals. Prograf^®^ (hard capsules containing tacrolimus in commercially available strengths) should be taken orally twice daily at 12-hour intervals, morning and evening, on an empty stomach; dosing according to the Summary of Product Characteristics.

